###### Augmented sample

A similar recruitment approach will be adopted for the augmented sample to ensure comparability with the main sample on demographic characteristics and source of recruitment.

Inclusion criteria
Children (aged 7+ years), young people and adults with ASD.Parents/carers, teachers and clinicians of individuals with ASD.Partners/caregivers/relatives/partners and employers of adult individuals with ASD, when parents and teachers are not relevant or appropriate.Adults lacking capacity to consent will be included in the instrument validation stage of the study as long as informed consent for their participation is obtained from a legal guardian/personal consultee.

Exclusion criteria
If researchers have doubts about a participant's capacity to consent after completing a capacity checklist, and an appropriate personal consultee cannot be identified, they will not be consented into the study. Doubts regarding capacity to consent will be discussed with the CI.If children, young people, or adults with ASD are not able to (or expected to not be able to) complete questionnaires, they will be excluded from the study. Discussions with clinicians involved in the patients’ usual care/caregivers/the patient themselves prior to consent will be used to explore the individual's ability to complete questionnaires, and the levels of distress it would potentially cause them.Participants who do not have a reasonable level of English will be excluded from the instrument validation stage of the study. This is because a reasonable level will be required to complete questionnaires which will only be available in English at the validation stage.

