### Aim

This protocol outlines the intended development and validation of the ‘Assessment of Concerning Behaviour Scale’ (ACB). The term ‘concerning behaviour‘ was chosen for the title of the questionnaire based on feedback from patient and public involvement panels (PPI panels; including parents of individuals with ASD and individuals with ASD) who disliked the use of the other terms including ‘psychopathology’, ‘abnormal behaviour’, ‘maladaptive behaviour’, ‘symptoms’, ‘challenging behaviour’ and ‘mental health problems’.

The ACB aims to be a multidimensional screening measure of concerning behaviours in ASD. The measure is not intended as a diagnostic tool of co-occurring conditions, but aims to identify the presence of symptoms that may require further, more in-depth assessment. The measure will assess the severity of concerning behaviours to allow for assessment of symptom severity and treatment response over time. It is intended primarily for clinical use, but will also be appropriate for use as an outcome in clinical trials.

The study aims to develop self-report, parent/carer, teacher/employer and clinician report versions that can be used across the lifespan and spectrum of intellectual ability. The aim is to make the resulting questionnaire approximately 40 questions in length that should not take longer than 20 min to complete.

This project is being conducted as part of a larger National Institute for Health Research (NIHR)-funded research project entitled ‘Improving Autism Mental Health’, reference number: RP-PG-1211-20016.

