Participants who do not have a reasonable level of English; a reasonable level of English, will be required to engage in the focus group/cognitive interviews.Individuals with ASD who are not verbal will not be included in focus groups/interviews. However, carers, teachers and parents of that person may still take part in their respective groups if they wish.Adults lacking capacity to consent will not be included in focus groups/interviews.If children, young people, or adults with ASD are not able to (or expected to not be able to) partake in the focus groups, they will be excluded from the instrument development stage. Discussions with clinicians involved in the patient's usual care/caregivers/the patient themselves prior to consent will be used to explore the individual's ability to partake in focus groups, and the levels of distress it would potentially cause them.

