##### Phase 2 sample size

###### Main sample

For this stage of the study, we will aim to recruit 200 people with ASD (approximately 100 adults and 100 children), in addition to their parent/carer/partner, teacher/employer and clinician, to complete the ACB and gold standard measures for analysis of reliability and validity of the ACB (see table 1). In a population cohort of people with ASD, the approximate IQ distribution was as follows: 15% had IQ<50, 40% had 50<IQ<70, 40% had an average IQ (70<IQ<115) and 5% had an above average IQ (IQ>115).^18^ We will aim to recruit across the spectrum of IQ in similar proportions to this population sample to provide a representation of a ‘typical’ ASD population, and ensure generalisability of findings. Attempts will be made to obtain estimates of IQ for individuals with ASD from school/medical notes. However, where this is not available, the research team will collect a brief measure of IQ through completing the Wechsler Abbreviated Scale of Intelligence^27^ during brief home visits to participant homes. All parents, caregivers, relatives and partners will be asked to provide an estimate of the cognitive functional age of the individual with ASD on their demographic questionnaire.

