#### Augmented sample

In order to permit a factor analysis of the items with the measure, we will augment the main sample with a further 150 children with ASD and 150 adults with ASD who will complete the ACB only. Where possible, parents/carers, teachers/employers and clinicians will also be recruited into this augmented sample, and asked to complete the appropriate version of the ACB. This augmented sample will be combined with the main sample to ensure that there will be at least six respondents per item for both the child and adult versions of the ACB for the factor analysis.

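### The Phase 2 exclusion of people who cannot complete questionnaires is study-wide, so the informant versions of the ACB would be evaluated only in people judged able to self-report

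*Protocol article*

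**What the plan says.** All points are from the protocol article.

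- **Exclusion criterion (Phase 2 recruitment, list under Augmented sample).** If people with ASD "are not able to (or expected to not be able to) complete questionnaires, they will be excluded from the study". Ability is judged before consent, in discussion with clinicians, caregivers or the person. The Main sample recruitment text refers forward to this list for its criteria, so it governs both samples.
- **Aim.** The study is to "develop self-report, parent/carer, teacher/employer and clinician report versions that can be used across the lifespan and spectrum of intellectual ability".
- **IQ target (Phase 2 sample size, Main sample).** In the reference cohort "15% had IQ<50, 40% had 50<IQ<70, 40% had an average IQ (70<IQ<115) and 5% had an above average IQ (IQ>115"). The plan then states: "We will aim to recruit across the spectrum of IQ in similar proportions to this population sample". The reason given is representativeness and generalisability.
- **Numbers.** In the main sample, "we will aim to recruit 200 people with ASD (approximately 100 adults and 100 children"), together with their informants. The augmented sample adds "a further 150 children with ASD and 150 adults with ASD who will complete the ACB only", with informants where possible.
- **Phase 1 contrast.** People who are not verbal are left out of focus groups and interviews, but "carers, teachers and parents of that person may still take part in their respective groups if they wish". The Phase 2 criteria contain no such sentence.
- **Provisions that widen entry to Phase 2.** Adults lacking capacity may enter through a guardian or consultee. Telephone and paper completion are offered. A proxy may complete the treatment report form for an adult who cannot.

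**The concern.** The criterion turns on what the person with ASD can do, but its consequence reaches every version of the instrument. Where a parent, teacher and clinician could all rate someone who cannot complete a questionnaire, the rule as written loses those ratings too.

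Reliability, factor structure and ROC results for the informant versions would then rest only on people judged able to self-report. Those who cannot self-report can be assessed only through an informant version, and they would contribute no data to its evaluation. Recruiting more people under the same rule does not repair this.

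**Working it through.** **1. The passages side by side.**

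| Place | Who is covered |
|---|---|
| Aim | All versions, whole range of intellectual ability |
| Phase 2 sample size, Main sample | IQ bands in roughly population proportions |
| Phase 1 exclusion criteria | Person who is not verbal left out; informants explicitly kept |
| Phase 2 exclusion criteria | Person unable to complete questionnaires excluded from the study; nothing said about informants |

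The consultee route settles consent; it does not lift the completion criterion. The proxy route covers the treatment report form only.

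**2. The plan's own target.** The bands sum to 100%: 15 + 40 + 40 + 5. The document states shares, not headcounts, so there is no stated count to reproduce.

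- Main sample: 0.15 × 200 = 30 with IQ below 50 (about 15 adults and 15 children).
- Combined sample: 200 + 300 = 500, and 0.15 × 500 = 75, if the augmented sample matches on IQ as the protocol attempts.

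**3. Effect of the criterion.** Let f be the fraction of the IQ<50 band who cannot complete questionnaires. The document gives no value, so f is an assumption, shown from 25% to 100%. Assume also that exclusions fall only in this band and that recruitment follows the eligible pool. The remaining share with IQ below 50 is

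0.15(1 − f) / [0.15(1 − f) + 0.85].

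| f | Share with IQ<50 | Of 200 (target 30) |
|---|---|---|
| 25% | 0.1125 / 0.9625 = 11.7% | about 23 |
| 50% | 0.0750 / 0.9250 = 8.1% | about 16 |
| 75% | 0.0375 / 0.8875 = 4.2% | about 8 |
| 100% | 0 / 0.85 = 0% | 0 |

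**4. Effect of the remedy on the factor analysis.** The Augmented sample section promises at least six respondents per item for the child and for the adult versions. Each age group has 100 + 150 = 250 people. At the roughly 40 items aimed for, 250 / 40 = 6.25. Six per item needs 240 respondents, so the margin is 10 / 250 = 4%.

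If people unable to self-report were included within the same totals, and the IQ target were met, the share without self-report would be 0.15f:

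| f | Without self-report | Self-reports per age group | Per item (40 items) |
|---|---|---|---|
| 25% | 3.75% | 240.6 | 6.02 |
| 50% | 7.5% | 231.3 | 5.78 |
| 100% | 15% | 212.5 | 5.31 |

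So the six-per-item figure survives for self-report only at the low end of the range.

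**The case against.** The strongest counter-argument is a narrower reading. The inclusion list names parents/carers, teachers and clinicians as participants in their own right, and Phase 1 excludes the person with ASD from a stage while letting informants continue. On that reading the Phase 2 rule removes the person only as a respondent. This may be what was intended, but the text does not say it. Phase 1 needed an explicit sentence to keep informants, and Phase 2 has none. The sample size section counts people with ASD, with informants attached to them, and the exclusion is from the study.

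Other objections limit how far the point goes, and they stand:

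- A reader might infer that the rule removes everyone with severe intellectual disability. It sets no IQ or severity threshold. Ability is judged individually, and telephone, paper and consultee routes would keep some people in. Recruitment also extends to autism-specific schools and residential settings.
- A reader might infer that all non-verbal people are lost. That exclusion belongs to Phase 1 focus groups and interviews and is not repeated in Phase 2; being non-verbal is not the same as being unable to complete a questionnaire.
- A reader might conclude that the IQ target cannot be met. It is worded as an aim, and about 30 people with IQ below 50 might be found by targeted recruitment among those able to complete with support. The remaining problem is who those 30 would be.
- Nothing in the criterion implies that the 50–70 band is excluded, so no loss is claimed there.
- The Introduction justifies multiple informants by the distinct information each gives, not as a substitute for self-report. The point therefore rests on the conflict with the stated aim and IQ target, not on a supposed purpose of the informant versions.

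**Conclusion.** The conflict is in the current text. As written, the criterion confines evaluation of every version, informant versions included, to people judged able to self-report, while the Aim and the IQ target claim a wider population.

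Under the assumptions in the working, the IQ<50 group in the main sample would fall from about 30 to somewhere between 23 and 0. Zero is the upper bound on the loss, not an expectation. The selection problem does not depend on these figures: even if the count were met, the retained group would be more able than the band it represents, and the informant versions would be untested in people who cannot self-report. The matter should be corrected; it does not undermine the findings for those who can complete the questionnaires.

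**What to change.** Limit the exclusion to the self-report version. People who cannot complete questionnaires would enter through the parent/carer, teacher/employer and clinician versions where consent or a consultee is in place, and would be excluded only if no informant can respond. If the sponsor prefers to keep the exclusion as it is, narrow the population claims in the Aim and in the Phase 2 sample size section to people able to complete questionnaires.

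The change is an amendment to one criterion. Its cost is that self-report is missing by design for some participants, so self-report analyses would have fewer than 200 in the main sample and fewer than 500 combined. The six-respondents-per-item figure should then be restated for the self-report versions, since at about 40 items it fails once more than about 4% of an age group lack self-report. Alternatively, recruitment could be raised to keep it.

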##### Phase 2 sample size

###### Main sample

For this stage of the study, we will aim to recruit 200 people with ASD (approximately 100 adults and 100 children), in addition to their parent/carer/partner, teacher/employer and clinician, to complete the ACB and gold standard measures for analysis of reliability and validity of the ACB (see table 1). In a population cohort of people with ASD, the approximate IQ distribution was as follows: 15% had IQ<50, 40% had 50<IQ<70, 40% had an average IQ (70<IQ<115) and 5% had an above average IQ (IQ>115).^18^ We will aim to recruit across the spectrum of IQ in similar proportions to this population sample to provide a representation of a ‘typical’ ASD population, and ensure generalisability of findings. Attempts will be made to obtain estimates of IQ for individuals with ASD from school/medical notes. However, where this is not available, the research team will collect a brief measure of IQ through completing the Wechsler Abbreviated Scale of Intelligence^27^ during brief home visits to participant homes. All parents, caregivers, relatives and partners will be asked to provide an estimate of the cognitive functional age of the individual with ASD on their demographic questionnaire.

#### Augmented sample

In order to permit a factor analysis of the items with the measure, we will augment the main sample with a further 150 children with ASD and 150 adults with ASD who will complete the ACB only. Where possible, parents/carers, teachers/employers and clinicians will also be recruited into this augmented sample, and asked to complete the appropriate version of the ACB. This augmented sample will be combined with the main sample to ensure that there will be at least six respondents per item for both the child and adult versions of the ACB for the factor analysis.

### Analysis strategy

#### Instrument development

Data collected during focus groups will be recorded and transcribed verbatim. Thematic analysis and content analysis will be used to organise focus group data into meaningful themes. The NVivo software package will be used to manage qualitative data generated from participant focus groups. The data analysis will follow the six steps to thematic analysis proposed by Braun and Clarke.^23^

#### Instrument validation

Quantitative data will be analysed using the SPSS and the MPlus statistics packages.

##### Reliability

###### Internal consistency

Cronbach's α values will be calculated for the total scale and subscales identified by factor analysis. α Values of 0.80, or higher, are commonly accepted as evidence of adequate internal reliability. An ‘if item deleted’ analysis will be conducted to identify whether any items should be dropped from the scale.

###### Test–retest reliability

To assess test–retest reliability, intraclass correlation coefficients will be calculated on subscale and total scores which are expected to remain stable. As this is an exploratory study, weighted Cohen's κ values will be also calculated to assess test–retest reliability at the item level. Coefficients will be established separately for children and adults, and also for parent/carer/relative/partner, teacher/employer and clinician reports on samples of approximately 50 questionnaires completed approximately 1 week after initial completion. For scores that are expected to remain stable, we anticipate a high intraclass correlation of 0.80, for which a sample of 37 would provide a 95% CI of width 0.2. Intraclass correlation coefficients will also be calculated to assess the longer term stability of the measure 4–6 months after initial completion of the questionnaire.

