All participants will be asked to complete the questionnaire battery twice: at study entry and again between 4 and 6 months after initial completion. This is to allow for analysis of the stability of the questionnaire. Based on clinical experience, 4–6 months was chosen as an appropriate period of time in which one would anticipate change in symptoms (eg, in relation to treatment response). Information on treatment, diagnoses and other relevant information will be gleaned from medical records in order to estimate when change of scores would be expected.

Approximately 50 participants, along with their parent/carer/relative/partner, teacher/employer and clinician will be asked to complete the ACB and gold standard questionnaires (see table 1) again, 1 week after their initial completion, to provide a measure of test–retest reliability. However, interim analyses will be conducted after 25 participants have completed the measure at 1 week. If a statistically significant correlation is evident, no further participants will be asked to complete measures again after 1 week. Since some of the items measured in the ACB are likely to be related to changeable constructs, a priori decisions will be made about items in the ACB that are expected to remain stable over 1 week.

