##### Phase 2 recruitment

###### Main sample

Individuals with ASD (children, young people and adults) and their parents/caregivers/relatives/partners, teachers/employers and clinicians will be invited to take part (see below for inclusion criteria). Individuals with ASD will be recruited via clinician/researcher invite as well as via poster advertisements within healthcare and community settings, social media and websites for ASD support groups. Individuals with ASD will also be recruited from autism-specific schools and residential settings. Researchers will primarily be recruiting participants via clinics within participating trusts; the aim is to recruit approximately 75% via this method. This is to ensure access to medical notes for as many participants as possible. However, participants will not be excluded if they are not currently under the care of participating trusts. Parental consent will be obtained to request details about the child's IQ, educational attainment and diagnosis from school records.

Parents of children with ASD will be asked to provide details of their child's teacher and clinician, and will provide consent for the research team to contact them and invite them to complete the study questionnaires. Adults with ASD will be asked to provide details of another person who knows them well (either a parent/caregiver/relative/partner) who would be able to complete a questionnaire about them. Adults with ASD will also be asked to provide contact details for their clinician and their employer (if applicable and appropriate).

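### The retest sample of about 50 for teacher/employer reports makes no allowance for adults without a reporting employer, and leaves few employer pairs

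*Protocol article*

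**What the plan says.** All places are in the protocol article.

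- **Test–retest reliability:** coefficients are planned separately for children and adults, "also for parent/carer/relative/partner, teacher/employer and clinician reports on samples of approximately 50 questionnaires". The precision statement is that "we anticipate a high intraclass correlation of 0.80, for which a sample of 37 would provide a 95% CI of width 0.2".
- **Phase 2, Main sample (design):** "Approximately 50 participants, along with their parent/carer/relative/partner, teacher/employer and clinician will be asked to complete the ACB" and the reference questionnaires "again, 1 week after their initial completion, to provide a measure of test–retest reliability". The section adds that "interim analyses will be conducted after 25 participants have completed the measure at 1 week", and retesting ends there if the correlation is statistically significant.
- **Phase 2 sample size, Main sample:** about 100 adults and 100 children are sought, "in addition to their parent/carer/partner, teacher/employer and clinician, to complete the ACB and gold standard measures".
- **Phase 2 recruitment, Main sample:** adults are asked for "contact details for their clinician and their employer (if applicable and appropriate").
- **Phase 2 inclusion criteria:** employers of adults are admitted where a parent or teacher is not a relevant or suitable informant.
- **Table 1:** teachers and employers have separate columns and complete different Achenbach forms (the CBCL Teacher Report and the ABCL respectively).

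The documents give no employment rate, no expected number of employer reports and no child/adult split of the retest sample.

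**The concern.** The teacher/employer class is given the same retest size as the other informant classes, although it alone depends on whether an adult has a job and whether contacting the employer is appropriate. About 50 participants can produce about 50 teacher/employer pairs only if almost every retested adult has a reporting employer or a teacher.

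Two things are at stake. If the class is analysed as one, its coefficient rests on fewer pairs than stated and describes teachers rating children more than employers rating adults. If it is split, the employer coefficient may be too imprecise to interpret, while the text still attaches the general sample size and CI width to it.

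**Working it through.** **Inputs from the protocol article.** Retest sample about 50 participants; two occasions (k = 2); anticipated intraclass correlation r = 0.80; target 95% CI width w = 0.2; stated n = 37.

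**Assumptions.** An even split of 25 children and 25 adults, following the roughly equal main sample. Every child has a teacher report, which is generous. No adult has a teacher. A share e of adults has a reporting employer, varied from 10% to 50%.

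**1. The plan's own figure.** The usual approximation is n = 8z²(1−r)²(1+(k−1)r)² / [k(k−1)w²] + 1.

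With z = 1.96: 8 × 3.8415 × 0.04 × 3.24 / (2 × 0.04) + 1 = 50.8, so 51 pairs. Fisher's z gives 54 to 56 and the exact F interval 54. The stated 37 is therefore not reproduced for a 95% CI with two occasions. At 37 pairs the exact F interval is 0.647 to 0.891, a width of 0.245. The same approximation does give 37 for a 90% CI.

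**2. Pairs in the combined class.** Employer pairs = 25e; total = 25 + 25e; teacher share = 25/(25 + 25e).

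| e | Employer pairs | Total pairs | Teacher share |
|---|---|---|---|
| 10% | 2.5 | 27.5 | 91% |
| 20% | 5 | 30 | 83% |
| 30% | 7.5 | 32.5 | 77% |
| 50% | 12.5 | 37.5 | 67% |
| 100% | 25 | 50 | 50% |

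The total reaches 50 only at e = 100%. It reaches even 37 only when e is at least 12/25 = 48%. For another split with a adults, the total is 50 − a(1 − e), so the shortfall is always the number of retested adults without a report.

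**3. Precision.** The exact F interval for two occasions has lower limit (A−1)/(A+1), with A = 9/F(0.975; n−1, n), and upper limit (B−1)/(B+1), with B = 9 × F(0.975; n, n−1). Here 9 = (1+0.80)/(1−0.80).

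| Pairs | 95% CI | Width |
|---|---|---|
| 5 | 0.10 to 0.98 | 0.88 |
| 10 | 0.41 to 0.95 | 0.54 |
| 13 | 0.48 to 0.93 | 0.45 |
| 25 | 0.60 to 0.91 | 0.31 |
| 28 | 0.62 to 0.90 | 0.29 |
| 38 | 0.65 to 0.89 | 0.24 |
| 50 | 0.67 to 0.88 | 0.21 |

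The combined class (28–38 pairs) gives a width of about 0.24–0.29. The employer part at its best in the assumed range (13 pairs) gives 0.45. The teacher part alone has about 25 pairs and a width of 0.31, so it does not meet the target either.

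**4. Alternative reading: 50 adults retested separately.** Employer pairs = 50e, that is 5 to 25 for e from 10% to 50%, with widths from 0.88 down to 0.31. With 50 children retested as well, this needs about 100 retested participants, whereas the design section gives about 50.

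**5. Early stop at 25 participants.** An even split leaves 12.5 adults, and 12.5e is about 1 to 6 employer pairs.

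**The case against.** The strongest reply is that teacher/employer means whichever applies. The recruitment text and the inclusion criteria make employers conditional, and the augmented sample adds informants only where possible. This stands as far as recruitment goes: a reader might infer that the plan believes every adult has an employer, and it does not say so. What remains is that the retest count was not adjusted to match those conditions.

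A reader might also infer that a combined coefficient would be almost wholly teachers'. The documents do not support that. They give no employment rate, and under the even split the teacher share passes 90% only if e is below about 11%. Some adults may also have a teacher as informant, which would raise the total but is not quantified.

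Pooling itself is not certain. The separation of children from adults in the test–retest section can be read as covering informants too, and Table 1 keeps teachers and employers apart. On that reading dilution largely disappears, but the employer coefficient then rests on the few employer pairs alone.

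Finally, a reader might infer that the employer version would be presented as validated in its own right. The documents make no such claim: the Aim lists a single teacher/employer version, the psychometric properties are called initial, and the reliability sections call the study exploratory. An article may leave some reporting detail to a fuller plan, but the sample size for this class is stated here.

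**Conclusion.** The point holds for the stated sample size. Under the assumptions above, the teacher/employer class yields about 28–38 retest pairs instead of about 50, with 67–91% from teachers and about 3–13 from employers. On either reading of the test–retest section the employer information is thin: a minority of a combined coefficient, or a separate one whose 95% CI at 13 pairs runs from 0.48 to 0.93.

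The exact numbers depend on the assumed employer share and the even split. The direction does not: any retested adult with neither a reporting employer nor a teacher takes the count below 50. The failure of 37 to give a 95% CI of width 0.2 with two occasions depends on neither assumption.

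**What to change.** - Estimate and report teacher and employer test–retest coefficients separately, each with its number of pairs and its 95% CI.
- Restate the test–retest section so that about 50 questionnaires and the CI width of 0.2 are not claimed for the teacher/employer class, or for either part of it, unless the achieved number of pairs supports them. Moving the claim to teachers alone would not do, because an even split leaves only about 25 teacher pairs.
- Do not use 37 as the threshold. At r = 0.80 with two occasions, a 95% CI of width 0.2 needs about 51–56 pairs.
- Describe the employer results as exploratory.

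The cost is split tables, some rewording and a weaker claim for employer reports. No further recruitment is needed.

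### Test–retest precision is misstated: 37 participants measured twice give a 95% CI about 0.24 wide at ICC 0.80, not 0.2, and the meaning of the planned 50 needs to be settled

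*Protocol article*

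**What the plan says.** The test–retest paragraph under Reliability gives one precision calculation: "we anticipate a high intraclass correlation of 0.80, for which a sample of 37 would provide a 95% CI of width 0.2". It applies to scores expected to remain stable.

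The number of occasions comes from the Main sample section of Phase 2, where a subset completes the measures "again, 1 week after their initial completion, to provide a measure of test–retest reliability". That is two measurements per person.

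Two places bear on the size of the retest sample. The Main sample section says: "Approximately 50 participants, along with their parent/carer/relative/partner, teacher/employer and clinician will be asked to complete the ACB" a second time. It does not divide that number by age. It adds an interim look after 25 participants that may end retesting. The test–retest paragraph says "Coefficients will be established separately for children and adults", and also by type of informant, and goes on to speak of samples, in the plural, of about 50 questionnaires.

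**The concern.** Anticipated ICC, sample size, confidence level and width all stand in one sentence, and the number of occasions is fixed elsewhere in the article, so the statement can be checked directly. It does not check out.

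The sentence is the only quantitative support given for the size of the retest sample. Because 37 is well below 50, it implies that about a quarter of the retests (13 of 50) could be lost and the interval would still be 0.2 wide. A team relying on this could accept incomplete returns, for example from teachers, employers or clinicians, as adequate when they are not.

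Separately, the two statements about 50 do not fit together without further explanation, and the precision of each age-specific coefficient depends on which one governs.

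**Working it through.** **Inputs.** ICC r = 0.80, n = 37, 95% confidence and full width w = 0.2, all from the test–retest paragraph. k = 2 measurements per person, from the Main sample section. The interval is taken as two-sided.

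**Attempt to reproduce 37 (Bonett).**
n = 8 z²(1 − r)²[1 + (k − 1)r]² / [k(k − 1)w²] + 1
= 8 × 1.96² × 0.2² × 1.8² / (2 × 1 × 0.2²) + 1
= 8 × 3.8416 × 0.04 × 3.24 / 0.08 + 1 = 50.8, so **51**, not 37.

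**Width at n = 37 (Bonett).**
w = √{8 × 3.8416 × 0.04 × 3.24 / [2 × (37 − 1)]} = √(3.983 / 72) = **0.235**.

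**Width at n = 37 (exact one-way F interval).**
- F₀ = (1 + r)/(1 − r) = 1.8/0.2 = 9.
- Lower: 9 / F₀.₉₇₅(36, 37) = 9 / 1.930 = 4.663, and (4.663 − 1)/(4.663 + 1) = 0.647.
- Upper: 9 × F₀.₉₇₅(37, 36) = 9 × 1.936 = 17.42, and (17.42 − 1)/(17.42 + 1) = 0.891.
- Width **0.245**. The smallest n with a width of 0.2 or less is **54** (n = 53 gives 0.201, n = 54 gives 0.199).

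**Other methods.** At n = 37 the two-way F interval gives 0.247 and Fisher z gives 0.244 to 0.250. A simulation of 20,000 data sets gave a mean width of 0.250 and a median of 0.245. These methods need 54 or 55 participants for a width of 0.2.

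**Shortfall in the stated n.** 51/37 = 1.38 and 54/37 = 1.46, so 38% to 46% more than 37.

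**What would produce about 37.** Bonett's formula at 90% confidence with k = 2 gives 36.06, rounded up to 37 (width 0.197). At 95% with k = 3 it gives 35.6, rounded up to 36 (width 0.196 at n = 37). Neither matches a 95% interval with two occasions. With k = 2 and 95%, the exact F width at n = 37 falls to about 0.2 only when the ICC is about 0.84.

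**Precision under each reading of the 50** (r = 0.80, k = 2, 95%):

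| n per coefficient | Bonett | Exact F, one-way | Exact F limits |
|---|---|---|---|
| 50 | 0.202 | 0.208 | 0.67 to 0.88 |
| 37 | 0.235 | 0.245 | 0.65 to 0.89 |
| 25 | 0.288 | 0.305 | 0.60 to 0.91 |

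Fisher z gives up to 0.211 at n = 50 and up to 0.316 at n = 25. The row for 25 assumes that a total of 50 divides evenly between children and adults, by analogy with the roughly 100 and 100 in the main sample; the article does not state this split. The same row applies, before any division by age, if retesting ends at the interim look.

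**The case against.** The best defence is that 37 is not the planned sample. The plan is about 50, and at 50 per coefficient the width is 0.20 to 0.21, essentially what is promised. This stands, and it limits the consequence: if 50 is the number behind each coefficient, the design roughly meets its target and only the supporting figure is wrong. It does not make 37 right, and it removes the apparent margin between 37 and 50.

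A second defence is rounding: 0.235 and 0.245 both become 0.2 at one decimal. This is weak. A number as specific as 37 is offered as the sample size for that width, and a true 0.2 needs 14 to 17 more people.

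Third, no decision in the article turns on the width of this interval, 0.80 is an anticipated value and not a pass mark, and the estimates and intervals eventually reported will be unaffected by the planning figure. That is fair; what suffers is the justification of the sample and any judgement about acceptable losses.

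A reader might go further and infer that the age-specific intervals are certain to be about 0.3 wide, so that an observed 0.80 could not exclude about 0.60. The documents do not establish this. It requires reading the 50 in the Main sample section as a total and dividing it evenly, while the plural samples of about 50 questionnaires in the test–retest paragraph can equally mean 50 per coefficient. This is a conflict to reconcile, not a demonstrated shortfall.

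**Conclusion.** The precision statement is wrong as written. At ICC 0.80, with two occasions and a two-sided 95% interval, 37 participants give a width of about 0.24 (0.235 to 0.250 across the methods tried), and a width of 0.2 needs about 51 to 54 (55 by the most conservative variants). No standard method tried gives 37 on the stated inputs. The 90% result is a possible explanation, but the article does not show how the figure was obtained.

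The planned 50 or so just reaches the target if it is the number behind each coefficient, with nothing to spare for missing retests. If it is a total over both age groups, the age-specific width is about 0.3, on the assumption of about 25 per group. Which applies cannot be settled from the article.

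**What to change.** 1. In the test–retest paragraph, replace 37 with about 51 to 54, or keep 37 and give the width as about 0.24. State the method and that two occasions are assumed.
2. Reconcile the Main sample section with the test–retest paragraph. Say whether the 50 or so retests apply to each age-group and informant coefficient (width about 0.20 to 0.21) or are a total over children and adults. If a total, restate the age-specific precision as about 0.3, with the assumed split.
3. Keep the child and adult coefficients separate. A pooled ICC should not be made primary to rescue the precision: the Augmented sample section refers to child and adult versions of the scale, and pooling can raise the ICC through differences between the groups.

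The first item costs only wording. So does the second if 50 is confirmed as a total, although the stated age-specific precision becomes less favourable. If 50 per age group is intended and only 50 in all had been scheduled, the additional retests can be drawn from the 200 main-sample participants already planned.
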